#### Recruitment

To maximize recruitment, the following strategies will be applied: (1) contacting grief and divorce-related associations as well as other potentially interested associations (eg, senior citizens’ associations), (2) contacting radio and television channels as well as newspapers, (3) distributing flyers in churches, beauty salons, and health-related institutions, (4) promoting the project in church administrations, (5) sending emails to large groups of university students, (6) promoting the study through social media, and (7) publishing an advert on research facility websites. To ensure an ongoing flow of participants until we reach the desired number of participants, we will continuously revise and rerun our recruitment strategy.

#### Eligibility Criteria

Participants meeting all the following inclusion criteria will be eligible for the study: (1) have experienced bereavement or separation, (2) either events must have happened more than 6 months prior to participating in the study, (3) feel the need for support to cope with the loss (a diagnosis of complicated grief is not necessary), (4) aged 18 years or older, (5) have regular access to the internet, (6) fluent in French, and (7) have approved the informed consent form.

The presence of any of the following exclusion criteria will preclude individuals from participating in the study: (1) moderate to acute current suicidality (Suicidal Ideation Attributes Scale score>19] [44,45]) (Note that participants having a Suicidal Ideation Attributes Scale score between 13 and 19 will undergo a telephonic interview to accurately assess their suicidal risk and will be excluded from the study if the risk is assessed as important [46]), (2) severe psychological or somatic disorders that need immediate treatment, (3) concomitant psychotherapy, (4) prescription or change in dosage of psychoactive drugs in the month prior to or during the self-help intervention, (5) inability to follow the study procedures (eg, due to comprehension problems), and (6) enrolment of the investigator, their family members, employees, and other dependent people.

### Security During the Procedure

During the intervention, participants will receive a biweekly assessment of the occurrence of a serious adverse event. Additionally, they will be able to contact the investigation team at any time through a contact form available in both the IBIs. An automatic reply will be sent informing that their message will be processed within 3 working days and that they can contact the emergency numbers that will be provided. This will enable the participant to make contact and be attended to at any moment if necessary. We will then discuss with them the reason for contacting us and if a serious adverse event is occurring. If this is the case, the participants will be contacted, and their situation will be evaluated. If necessary, alternative treatments will be proposed.

### Measures

The calendar for obtaining the measures from the participants can be found in Multimedia Appendix 1.

The feelings of loneliness will be measured with the University of California Los Angeles Loneliness Scale [62,63] contains 10 positive (eg, “I feel in tune with the people around me”) and 10 negative (eg, “I lack companionship”) items. Participants will respond to each item using a 4-point scale (1=never to 4=often).

Program satisfaction will be measured with a translated version of the Client Satisfaction Questionnaire adapted to IBIs [64]. The questionnaire will assess satisfaction with the theoretical content, practical content (exercises), structure, design, and overall assessment of the intervention. It contains 15 items rated with a scale ranging from 1 (no) to 4 (yes) and 4 open-ended questions.

Additionally, we will monitor the mood of the LIVIA 2.0 participants on a weekly basis using a single item: “How would you describe your current mood” on a scale ranging from 0 (very bad*)* to 6 (very good). Moreover, we will monitor weekly grief and solitude symptoms on a scale ranging from 0 (strongly disagree) to 7 (strongly agree) with the following items: “During the past 24 hours, (1) I have felt negative emotions; (2) I have had negative images or thoughts; (3) I felt blocked in my behavior (what I do, my activities); (4) I felt lonely; (5) I had a very clear vision of myself.” We will also assess the linguistic behaviors in the exercises of LIVIA 2.0 where the participants are required to describe a loss-related situation. More specifically, we will analyze indicators of verbal immediacy (use of first-person pronouns and present-tense words) and so-called “we-talk” (first-person plural pronouns [39]). Finally, we will assess the degree of guidance required in each group (number of participants requiring guidance and number of emails exchanged).

#### Predictors and Moderators

The following variables will be assessed only at baseline (T0) and their moderating role in the efficacy of the intervention will be explored: (1) demographic characteristics (31 items); (2) relationship quality prior to death or separation, measured with adapted items from the Dyadic Adjustment Scale-4 [65,66]. The Dyadic Adjustment Scale-4 will only be used if the person lost was a romantic partner. It has 4 items, with 3 items (eg, “In general, how often do you think that things between you and your partner are going well?”) rated on a 6-point scale (from 0=all the time to 5=never) and a 4th item rated on a 7-point scale (from 0=extremely unhappy to 6=perfectly happy); (3) adult attachment style, measured with the Experiences in Close Relationships–Short Form scales [67,68]. This 12-item measure captures variability along two attachment dimensions: avoidance and anxiety. Participants will rate the extent to which they agreed with each statement using a 7-point scale (1=strongly disagree to 7=strongly agree); (4) interpersonal closeness with the person lost measured with the Inclusion of Other in the Self scale [69]. Respondents will be required to select 1 out of 7 Venn-like diagrams depicting their relationship with the lost person.

### Data Collection and Management

Study data will be collected and managed using REDCap electronic data capture tools hosted at the Lausanne University Hospital [41,42]. REDCap is a secure, web-based software platform designed to support data capture for research studies, providing (1) an intuitive interface for validated data assessment, (2) audit trails for tracking data manipulation and export procedures, (3) automated export procedures for data downloads to common statistical packages, and (4) procedures for data integration and interoperability with external sources. Data integrity is enforced through several mechanism (ie, referential data rules, valid values, range checks, and consistency checks).

Moreover, data on the use of the self-help sessions will be collected within the platform, as well as the entries of the participants in LIVIA 2.0 (exercises, quizzes, questions, etc). All data will be saved anonymously, identified only by a random code. The servers are protected by high-end firewall systems. The participant code list will be saved on an internal Network-Attached Storage. Only the researchers directly involved in the study will have access to the data.

### Statistical Analysis

Primary analyses will be performed using SPSS (IBM Corporation) and R (R Foundation for Statistical Computing) after the participants complete the study. Primary follow-up analyses will be conducted 3 months later. Intermediate analyses during data collection will be done. We will perform intention-to-treat analyses [70]. We will develop multilevel mixed effects models with repeated measures data in SPSS to evaluate the efficacy of LIVIA 2.0 compared to LIVIA 1 and the stability of the effects. These models have the advantages of considering the dependency of the data and accounting for the correlation of repeated measures within individuals. Moreover, they rely on all available data of every participant and estimate parameters of missing values [71].

We will explore the potential moderating effect of different variables on the intervention effects by conducting analyses of covariance for repeated measures. To explore the short-term efficacy of each module, we will use multilevel modeling whereby each participant’s monitoring data are nested within participants. These analyses will be conducted with Mplus [72] or R. Additionally, we will analyze qualitatively the satisfaction questionnaire using the thematic content analysis method [73]. Finally, we will analyze the semantic content of the exercises included in LIVIA 2.0 [39] and test if some categories (eg, “we-talk”) are associated with the efficacy of the program. We will rely on a significance level of a 2-sided *α*=.05 or smaller. We will use the Bonferroni correction to adjust for multiple testing.

To handle missing data and dropouts, we will conduct the analyses relying on the intention-to-treat paradigm. We will first analyze the magnitude of missing data, explore the missing data patterns, and determine the pattern of missing data (missing completely at random, missing at random, and not missing at random). If the missing mechanism is missing at random, we will use multilevel regression analyses, which allow for nonindependent observations and for different numbers of measurement points per participant and are thus less sensitive to missing data [71].

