### Assignment of Interventions

To assign participants to the LIVIA 2.0 (experimental) or LIVIA 1 (control) condition, we will use the randomization module in REDCap (Research Electronic Data Capture [41,42]), which will automatically generate a 1:1 randomization. We will apply a single-blinded randomization strategy stratified according to the gender and loss type (bereavement vs separation) of the participants. Due to the nature of the study, double-blinded randomization is not possible.

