### Participants

#### Sample Size

We will conduct a power analysis with G*Power (Version 3.1.9.2 [43]) for ANOVA of repeated measures involving within-between interactions that would enable us to compare the efficacy of the 2 interventions. Based on a probability level of 0.05 and a power of 0.8, to detect a small effect size of *f* =0.1 (as we expect small differences between the 2 programs), a sample size of 164 participants is needed. Expecting a dropout rate of 30% at the 3-month follow-up, we aim to have 234 participants at posttest.

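### The arm comparison is sized on a group-by-time interaction with the pretest as an outcome; using the pretest score for adjustment would give a more precise arm difference at almost no cost

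*Protocol article*

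**What the plan says.** The Sample Size section names the test on which the trial is sized, "ANOVA of repeated measures involving within-between interactions that would enable us to compare the efficacy of the 2 interventions". Its inputs are introduced with "Based on a probability level of 0.05 and a power of 0.8", the effect size is f = 0.1 ("as we expect small differences between the 2 programs"), and the result is "a sample size of 164 participants is needed". The correlation between visits is not given. Design and Procedure sets three measurement points: T0 (pretest), T1 (posttest) and T2 (follow-up).

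The Statistical Analysis section then states: "We will develop multilevel mixed effects models with repeated measures data in SPSS to evaluate the efficacy of LIVIA 2.0 compared to LIVIA 1". It does not list the fixed effects or covariates, say how T0 enters the model, or name the deciding contrast. Analysis of covariance appears there only for the exploratory moderator analyses.

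Under Assignment of Interventions, randomisation is 1:1 and "stratified according to the gender and loss type (bereavement vs separation) of the participants".

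**The concern.** In a group-by-time interaction over T0, T1 and T2, the pretest is one of the outcomes and its mean is free to differ between arms. The arm effect is then in essence a difference in change from baseline. It carries the full sampling noise of the chance baseline difference, although the two arms come from the same population before treatment. A model that conditions on T0, or holds the T0 means equal, uses that fact and estimates the same arm difference with a smaller standard error.

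At stake is precision in a trial that expects small differences and 30% dropout. The T0 scores will be collected anyway, and neither the sizing nor the analysis text says that they will be used to gain precision.

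**Working it through.** **Inputs.** From the article: f = 0.1, alpha 0.05, power 0.8, two arms (1:1), three visits, N = 164, 30% dropout. Not in the article: the correlation ρ between visits. I assume equal correlations (compound symmetry), take ρ = 0.5 as the value that reproduces N, and show a range.

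**1. The plan's own figure.** For the interaction, λ = N·m·f²/(1−ρ) with m = 3, on 2 and (N−2)·2 degrees of freedom.
- N = 164, ρ = 0.5: λ = 164 × 3 × 0.01 / 0.5 = 9.84, on 2 and 324 df, power 0.805. N = 164 is the exact match.
- Variants that do not match: three visits with ρ = 0.3 gives 228, with ρ = 0.7 gives 98; two visits with ρ = 0.5 gives 200.
- Dropout: 164/0.7 = 234.3, stated as 234.

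The sized test is therefore the 2-df interaction over T0, T1 and T2.

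**2. Variance of the arm difference** (in units of 4σ²/N, complete data).
- One visit. Change from baseline: 2(1−ρ). Baseline-adjusted: 1−ρ². Reduction: (1−ρ)/2. At ρ = 0.5: 1.00 against 0.75, a cut of 25%.
- Mean of T1 and T2. Change: (1+ρ)/2 + 1 − 2ρ = 1.5(1−ρ). Baseline-adjusted: (1+ρ)/2 − ρ². Reduction: 2(1−ρ)/3. At ρ = 0.5: 0.75 against 0.50, a cut of 33%.

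| ρ | one visit | T1/T2 mean |
|---|---|---|
| 0.3 | 35% | 47% |
| 0.5 | 25% | 33% |
| 0.6 | 20% | 27% |
| 0.7 | 15% | 20% |
| 0.8 | 10% | 13% |

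Both reductions are positive for every ρ below 1.

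**3. Dropout.** Generalised least squares for a free-baseline and a constrained-baseline mixed model, keeping every T0 score, ρ = 0.5, 30% lost by T2:
- half lost before T1 and half between T1 and T2: 22% at T1, 19% at T2, 28% for the mean;
- all lost before T1: 19% at T1 and at T2, 26% for the mean.

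**4. Unequal correlations.** If the correlation decays (adjacent visits r, T0 with T2 r²), r = 0.5 gives 25% at T1, 37.5% at T2 and 39% for the mean; r = 0.8 gives 10%, 18% and 17%.

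**5. Gender and loss type.** Added as main effects to the free-baseline model, they change the variance of the group-by-time contrast by 0.0%, because effects that are constant over time cancel within a person. All of the gain in steps 2 to 4 comes from baseline.

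**6. Gain for the same 2-df test.** Take an equal effect at T1 and T2. Then f = 0.1 means d = 0.1 × √18 = 0.424, so d² = 0.18, and N/4 × d² = 41 × 0.18 = 7.38.
- Free baseline: 7.38 × 4/3 = 9.84.
- Baseline used: 7.38 × 2 = 14.76. About 110 evaluable participants would then give 80% power at alpha 0.05, instead of 164.

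This is the favourable pattern. If the same f = 0.1 comes from an effect at T1 only (again d = 0.424), the noncentrality rises only from 9.84 to 7.38 × 1.5 = 11.07.

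**The case against.** The strongest reply is that the article does not state the model under criticism. Its wording fits a constrained-baseline or stratum-adjusted model just as well; the free baseline is inferred from the sizing test; and a condensed article commonly leaves covariates and contrasts to the full protocol or SAP, which are not shown. This stands in part. A reader might infer that the analysis excludes the pretest or the strata, and the documents do not support that. But the Sample Size section does say which test compares the two programs, and a better use of data already collected exists. The recommendation does not rest on silence alone.

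Three further inferences also fail.
- **That omitting the strata makes the standard errors wrong, or that the strata supply part of the 25-33%.** Step 5 shows no contribution for time-constant effects. In a baseline-adjusted model their extra gain depends on how prognostic they remain, which the article does not say.
- **That baseline adjustment alone lifts power from 0.665 to 0.76 or 0.92.** These figures assume N = 164, d = 0.424 at both visits and alpha 0.05/3 = 0.0167, which takes Bonferroni over the three primary outcomes; the article names no family. An unadjusted 1-df contrast (T1/T2 mean minus T0) and a baseline-adjusted T1 contrast both have noncentrality 9.84 and power about 0.76, so the first step is only the move from 2 df to 1 df. The 0.92 belongs to the adjusted T1/T2 mean and needs equal effects at both visits. If f = 0.1 comes from T1 alone, that mean has power 0.31, against 0.665 for the interaction.
- **That the interaction is unsuitable because it can reject in favour of LIVIA 1.** Any two-sided test can do so, and the article plans two-sided testing. It also aims to assess whether effects are stable, which a multi-visit model can address.

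**Conclusion.** The point holds as an efficiency recommendation. The comparison is sized on an interaction that treats the pretest as an outcome, and the analysis text states no use of the pretest to gain precision. Relative to the change-from-baseline contrast, using it cuts the variance by 25% (one visit) to 33% (T1/T2 mean) at ρ = 0.5. Over ρ from 0.3 to 0.8 the range is 35%/47% down to 10%/13%, and at ρ = 0.5 with 30% loss it is about 19-28%. The size rests on a correlation that the article does not give and, apart from step 4, on compound symmetry. The direction of the gain does not depend on the value of ρ.

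A reader might infer that the planned test is biased or invalid. It is neither. Which visit or average should be the primary contrast is a separate choice that depends on the expected time course, and the figures here do not settle it.

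**What to change.** In the Statistical Analysis section, state that for each primary outcome the arm difference at T1 and T2 is estimated from a mixed model that either adjusts for the T0 score or constrains the T0 means to be equal between arms. The constrained form also keeps participants who have only a T0 score, which suits the intention-to-treat aim. Include gender and loss type as covariates because randomisation is stratified on them; expect added precision only if they are prognostic after baseline adjustment. Choose the primary contrast separately, with a reason based on the expected time course, and fix it before any arm comparison is seen, including the intermediate analyses that the section mentions.

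The cost is a change of wording and a few degrees of freedom. T0 scores, gender and loss type are needed for the trial in any case, so there are no new data. The sample size can stay as it is, with the gain kept as a reserve.

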**Methods:**

Outcomes will be assessed at pretest, posttest (12 weeks later), and follow-up (24 weeks later). We will recruit 234 participants through a variety of means, including social media and contacts with the press. Primary outcomes are grief symptoms, depressive symptoms, and eudemonic well-being. Secondary outcomes are anxiety symptoms, grief coping strategies, aspects related to self-identity reorganization, and program satisfaction. LIVIA 2.0 participants will additionally undergo a weekly mood and grief symptom monitoring, allowing us to explore the short-term efficacy of the sessions.

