### Design and Procedure

This study is a monocentric, single-blinded, 2-arm RCT comparing the efficacy of 2 versions of an IBI—namely LIVIA 1 and LIVIA 2.0—aimed at relieving distress and augmenting the well-being of people suffering from prolonged grief symptoms. There will be three measurement points: a pretest (T0), posttest (T1), and follow-up (T2). The flowchart of the study design is presented in Figure 1.

This self-help intervention is embedded in a larger project on life-span vulnerabilities and strengths conducted by the LIVES Centre [40].

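### Single-step Bonferroni is valid, but Holm's step-down version rejects at least as much at the same family-wise error; the gain in power per primary outcome is about 6 to 9 points if all three respond, and less otherwise

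*Protocol article*

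**What the plan says.** The Methods part of the abstract lists the primary endpoints: "Primary outcomes are grief symptoms, depressive symptoms, and eudemonic well-being". The Statistical Analysis section sets the level, "We will rely on a significance level of a 2-sided *α*=.05 or smaller", and then the multiplicity rule, "We will use the Bonferroni correction to adjust for multiple testing". It names no step-down or other sequential procedure, and it does not say which tests form a family. The second main hypothesis under Objectives expects LIVIA 2.0 to do better than LIVIA 1 on every outcome.

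The Sample Size section sizes the trial for one test, an "ANOVA of repeated measures involving within-between interactions". The inputs are given as "Based on a probability level of 0.05 and a power of 0.8", "to detect a small effect size of *f* =0.1", leading to 164 participants, or 234 after allowing for 30% dropout.

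**The concern.** Bonferroni over three tests compares every p value with .05/3. Holm compares the smallest p value with .05/3, the next with .05/2 and the largest with .05, and stops at the first failure. Its first step is the Bonferroni test, so it loses no rejection that Bonferroni makes, and later steps can add rejections. Both hold the family-wise error at .05 whatever the correlation between outcomes.

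The article expects only small differences between the programmes and expects them on all outcomes. That is the setting in which the later steps of Holm matter most. A true effect on a second or third outcome could go undeclared only because the single-step rule was used.

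**Working it through.** **Inputs from the article.** Two arms ("automatically generate a 1:1 randomization"), three measurement points, f = 0.1, α = .05, power 0.8, N = 164, three primary outcomes.

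**Assumptions not in the article.** Correlation among repeated measures ρ = 0.5 and sphericity ε = 1 (G*Power defaults); the family is the three primary outcomes; between-outcome correlation r from 0 to 0.9.

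**Step 1: reproduce the plan's figure.** For the within-between interaction with k = 2 groups and m = 3 measurements:

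- λ = f² × N × m / (1 − ρ) = 0.01 × 164 × 3 / 0.5 = 9.84
- df1 = (k − 1)(m − 1) = 2; df2 = (N − k)(m − 1) = 162 × 2 = 324
- Power at α = .05 is 80.5%, and N = 164 is the smallest even number that reaches 80%. Then 164 / 0.7 = 234.3.

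The stated 164 is reproduced, which supports the assumed ρ and ε.

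**Step 2: Bonferroni.** The same F test at .05 / 3 = .0167 has power 66.5% at N = 164 and 84.7% at N = 234.

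**Step 3: Holm, all three outcomes at f = 0.1.** Three F tests were simulated with 400,000 replicates per setting. Power per outcome, with the gain over Bonferroni in points:

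| r | Holm, N = 164 | Gain | Holm, N = 234 | Gain |
|---|---|---|---|---|
| 0 | 75.7% | 9.2 | 91.6% | 6.9 |
| 0.3 | 74.8% | 8.3 | 90.8% | 6.1 |
| 0.5 | 74.2% | 7.7 | 90.2% | 5.6 |
| 0.7 | 73.5% | 7.0 | 89.6% | 4.9 |
| 0.9 | 72.4% | 5.9 | 88.5% | 3.9 |

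A separate large-sample run gave 5.5 points at N = 234 and r = 0.5. A one-degree-of-freedom version, set to 80% power at .05, gave gains of 5.7 to 9.2 points over the same correlations.

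**Step 4: fewer outcomes respond (N = 164, r from 0 to 0.7).**

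- Two respond: each gains 3.0 to 3.8 points.
- One responds: it gains 0.1 to 0.2 points.

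**Step 5: what does not change.**

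- The chance of at least one rejection is the same under both rules, because the first step is the same. At r = 0.5 with all three responding it is 88.3%.
- Family-wise error under the global null is also the same: 4.9%, 4.5% and 4.0% at r = 0, 0.5 and 0.7.
- When two outcomes respond, the third, null outcome is rejected in 3.7% to 3.8% of runs with Holm against about 1.7% with Bonferroni. Both are within .05.

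**The case against.** Bonferroni is prespecified, controls the family-wise error under any dependence and contradicts nothing in the article. That stands in full: nothing here shows bias or inflated type I error.

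Holm's advantage is confined to rejection decisions. Bonferroni has simple matching simultaneous confidence intervals and Holm does not. With unadjusted intervals, one can exclude zero beside a non-significant adjusted p value. That is a real trade-off, and investigators who value the intervals could keep Bonferroni.

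Three stronger readings might be inferred, and the documents do not support them.

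- *The plan gives away about 8 points on each primary outcome whatever happens.* That figure needs a true f = 0.1 on all three outcomes, a moderate correlation that the article does not give, and only 164 contributors. The mixed models are planned to use all available data from every participant, so 164 is the pessimistic end.
- *The relevant loss is the chance of winning on all three,* which at r = 0.5 and N = 164 goes from 42.0% to 59.5%. The article expects superiority on all outcomes but does not say that the three primaries must succeed jointly. If they had to, no split of alpha would be needed: testing each at .05 gives about 62%.
- *The family is the three primary outcomes.* The sentence on Bonferroni is general and defines no family. An article may leave that to the full protocol or analysis plan, so its absence is not criticised here.

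**Conclusion.** The point holds as an efficiency improvement. For rejection decisions the single-step rule is never better than Holm at the same family-wise error; this is a property of the procedures and does not rest on the simulation.

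The size does rest on assumptions: the three primaries as the family, G*Power's default ρ and ε, and an assumed range for r. On those terms the gain per outcome is about 6 to 9 points if all three respond with 164 contributors, and about 5.5 at r = 0.5 with 234 and no loss. With 164 contributors it is about 3 points each if two respond and about 0 if one does. There is no gain in the chance of at least one success.

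Nor does Holm restore the planned power. The sample size used an undivided .05, and at r = 0.5 Holm recovers 7.7 of the 14.0 points lost (80.5% to 66.5%), leaving power per outcome below 80% at N = 164.

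**What to change.** In Statistical Analysis, name the Holm-Bonferroni step-down procedure in place of the Bonferroni correction. Apply it within whatever families the plan already corrects, with a family-wise two-sided level of .05 in each. The change should not be used to redefine those families.

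The cost is one sentence, made before outcome data are analysed; the article reports that no data had been collected at submission. Recruitment, measures and models are unaffected. Because Holm lacks simple matching simultaneous intervals, report unadjusted 95% confidence intervals, labelled as unadjusted, beside the Holm-adjusted p values.
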